## Abstract

**Background:**

Disorders of consciousness (DoC) after severe acquired brain injury are difficult to diagnose at the bedside. The Coma Recovery Scale-Revised (CRS-R) is the behavioral reference standard, but raw scores can be affected by arousal fluctuation, motor impairment, sensory deficits, sedation, language disturbance, and local assessment conditions.

**Objective:**

This protocol describes a prospective validation study of a multimodal artificial intelligence (AI) system designed to standardize CRS-R scores by integrating routine electroencephalography (EEG), bedside CRS-R subscale scores, and selected clinical contextual variables against an adjudicated standardized reference.

**Methods and analysis:**

The study includes retrospective model development followed by prospective, blinded clinical validation at Guangdong Second Traditional Chinese Medicine Hospital. The locked model will use subscale-specific ordinal prediction modules and a rule-constrained integration layer to generate AI-standardized CRS-R subscale scores, total scores, diagnostic categories, uncertainty estimates, and prespecified case-level explanations. Prospective participants will undergo two independent bedside CRS-R assessments and routine scalp EEG within target and maximum assessment windows. A blinded expert committee will generate the reference CRS-R score using paired behavioral records, available videos, nursing observations, medication and confounder records. The primary endpoint is the participant-level reduction in absolute CRS-R total-score error after AI-assisted standardization relative to the adjudicated reference. Secondary endpoints include subscale agreement, diagnostic-category agreement, inter-rater variability, uncertainty-flag performance, workflow feasibility, and exploratory day-14 consciousness improvement.

**Ethics and dissemination:**

The protocol was approved by the Ethics Committee of Guangdong Second Traditional Chinese Medicine Hospital (approval number Z202603-004-01; review date March 25, 2026; approval validity March 27, 2026 to March 26, 2027). Results will be disseminated through peer-reviewed publication and academic presentations.

**Clinical Trial Registration:**

https://www.chictr.org.cn, Chinese Clinical Trial Registry, ChiCTR2600124984.

## Introduction

1

Disorders of consciousness (DoC) after severe acquired brain injury are diagnostically challenging and ethically consequential. Judgments about residual consciousness influence prognosis, rehabilitation referral, treatment escalation, and goals-of-care discussions (1–3). Current frameworks still place standardized behavioral examination at the center of DoC assessment, while acknowledging that electrophysiological and neuroimaging biomarkers have not yet been fully translated into routine bedside care (1, 3–5).

This gap matters clinically. In a prospective *New England Journal of Medicine* study, 60 of 241 patients without observable command-following (25%) showed cognitive motor dissociation on task-based EEG or functional magnetic resonance imaging (6). A critical care review estimated covert consciousness in approximately 15%–20% of ICU patients who appear behaviorally unresponsive (7). Sleep-spindle and multimodal biomarker studies further show that electrophysiological signals may precede or complement behavioral signs of recovery (8–10).

The CRS-R remains the behavioral reference standard, but raw scores are vulnerable to factors that can obscure purposeful behavior. These include aphasia, severe motor impairment, sensory limitation, fluctuating arousal, sedative exposure, body position, and inter-rater variation (1, 3, 11, 12). Repeated assessments are often needed because first-assessment misclassification remains common, and CRS-R thresholds may not perform identically across subscales, etiologies, and clinical settings (13–18).

EEG is attractive for CRS-R score standardization because it is bedside-compatible, repeatable, and increasingly supported by mature analytic pipelines. Neuromonitoring reviews also emphasize that continuous EEG and related bedside modalities can help detect neurological events that are otherwise difficult to observe in sedated or intubated patients (19). Recent studies have used deep learning, interpretable temporal-spectral modeling, dynamic EEG pattern analysis, and low-dimensional EEG representations to detect awareness or predict outcome in DoC (5, 20–26). Multimodal studies also suggest that behavior, electrophysiology, imaging, and clinical context provide complementary rather than interchangeable information (4, 27–29).

Most AI studies in DoC still focus on retrospective state classification or outcome prediction. A 2025 scoping review identified only 21 eligible peer-reviewed AI studies after screening 49,417 records, and recent reviews note that many models classify unresponsive wakefulness syndrome (UWS) vs. minimally conscious state (MCS) instead of preserving CRS-R subscale structure or prospectively validating human-in-the-loop deployment (11, 20, 30, 31). Prospective DoC research also requires explicit case ascertainment, outcome definitions, covariate capture, and timing of data acquisition because behavioral responsiveness is subtle and fluctuating (32). This protocol addresses that gap by evaluating whether an EEG-clinical AI system can standardize continuous CRS-R total and subscale scores against an adjudicated standardized reference.

In this protocol, AI-assisted CRS-R score standardization means generation of an adjusted subscale profile and total score using a locked model that incorporates raw bedside CRS-R subscale scores, EEG-derived features, and predefined contextual variables. The term does not refer to statistical calibration of predicted probabilities against observed outcome frequencies. The system is intended to support standardized review of bedside scores during validation, not to replace CRS-R examination or expert clinical judgment.

The study is reported as a prospective Study Protocol and is aligned with SPIRIT and SPIRIT-AI principles for protocols involving artificial intelligence (33). A completed SPIRIT and SPIRIT-AI checklist is provided as Supplementary Table S1. The protocol is also informed by TRIPOD+AI reporting principles for prediction model development and evaluation (34). It is designed to test a locked model under blinded, real-world clinical validation conditions rather than to replace clinician judgment during the validation stage.

## Methods and analysis

2

### Study design and setting

2.1

This is a two-stage study consisting of retrospective model development followed by prospective, blinded clinical validation. The study will be conducted at Guangdong Second Traditional Chinese Medicine Hospital. The clinical research unit named in the ethics approval is Guangdong Second Traditional Chinese Medicine Hospital, with implementation through the Department of Acupuncture and Rehabilitation, Huangpu Hospital District.

The primary aim is to determine whether AI-standardized CRS-R total scores show smaller absolute error than unstandardized bedside CRS-R total scores when compared with an adjudicated standardized reference. The secondary aims are to assess subscale-level agreement, diagnostic-category agreement, inter-rater variability, uncertainty-flag performance, workflow feasibility, and exploratory day-14 consciousness improvement.

### Study population

2.2

Adult inpatients with acquired disorders of consciousness will be screened during the recruitment period. Whenever applicable, the retrospective model-development and prospective-validation cohorts will follow the same prespecified inclusion and exclusion criteria, ensuring clinical alignment across study phases. Figure 1 summarizes the overall pathway from participant screening and multimodal data collection to locked AI-assisted score standardization, blinded adjudication, and endpoint analysis.

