#### Exclusion criteria

2.2.2

Participants will be excluded if any of the following applies:

Persistent deep sedation, general anesthesia, or uncontrolled status epilepticus during the assessment window.Complete paralysis from severe cervical spinal cord injury or peripheral neuromuscular blockade that prevents interpretation of CRS-R motor or oral motor subscales.Severe irreversible neurodegenerative disease or severe psychiatric disorder that would confound DoC diagnosis.EEG dominated by uncontrolled epileptiform activity or status epilepticus, preventing valid resting-state background or connectivity feature extraction.EEG recordings of insufficient quality despite repeat acquisition when repeat acquisition is clinically feasible.Massive bilateral skull defects preventing accurate and symmetrical scalp electrode placement according to the international 10–20 system.Concurrent severe systemic infection or metabolic disorder causing an acute, reversible decline in consciousness.Refusal or withdrawal of informed consent by the legally authorized representative.

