### Retrospective model development

2.3

The retrospective phase will establish the preprocessing pipeline, feature definitions, model architecture, missing-data rules, quality-control thresholds, and interpretability outputs before prospective enrollment begins. The model will be fully trained and locked before the first prospective participant is included.

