#### Internal validation and model locking

2.3.5

During retrospective development, model performance will be assessed using nested fivefold cross-validation with patient-level splitting. If a patient contributes more than one assessment episode, all episodes from that patient will remain in the same fold. The inner loop will tune hyperparameters on the training partition, and the outer loop will estimate generalization performance on held-out patients. EEG preprocessing decisions that use data-derived thresholds, feature scaling, imputation, feature selection, dimensionality reduction, model selection, uncertainty thresholds, and score-shift review thresholds will be learned or fixed within the training partitions only and then applied to the corresponding held-out fold. Model parameters, preprocessing rules, feature definitions, missing-data handling logic, uncertainty thresholds, review thresholds, software versions, and deployment checksums will be archived before prospective use. No parameter updating, threshold tuning, or online learning will be allowed during prospective validation.

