### Statistical analysis

2.10

All analyses will be prespecified and performed after prospective database lock. The primary analysis population will include participants with two blinded bedside CRS-R assessments, usable EEG according to protocol, and an adjudicated reference score. A feasibility population will include all consented participants.

Baseline characteristics will be summarized as mean and standard deviation or median and interquartile range for continuous variables, and as counts and percentages for categorical variables. The primary analysis will summarize *D*_*i*_ and test whether the mean participant-level error reduction differs from zero using a paired test appropriate to the empirical distribution. A linear mixed-effects model with participant as a random effect and method and rater as fixed effects will be used as a secondary sensitivity analysis to estimate rater-level effects. Intraclass correlation coefficients, mean absolute error, root mean square error, and Bland-Altman plots will be reported with 95% confidence intervals.

Diagnostic-category agreement will be assessed with weighted kappa, macro-averaged F1-score, sensitivity, specificity, and confusion matrices using the mapping rules in Table 1. Subscale-level performance will be assessed using ordinal agreement metrics, weighted kappa, and subscale-specific absolute error. Inter-rater variability before and after AI-assisted standardization will be compared using paired tests and mixed-effects models. The uncertainty module will be evaluated by testing whether high-uncertainty cases are enriched for large scoring error, rater disagreement, or reference-standard disagreement.

Confidence intervals for primary and major secondary metrics will be estimated using participant-level bootstrap resampling. Prespecified subgroup analyses will explore model performance across etiology, chronicity, tracheostomy status, severe motor impairment, and recent sedative exposure. Sensitivity analyses will exclude participants with substantial clinical changes between ratings, cases exceeding target timing windows, and cases with major sedation or airway changes during the assessment episode. A reduced-feature inference mode using report-level EEG variables only will also be tested.

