Several design features are intended to reduce avoidable bias. Paired independent CRS-R assessments will allow direct comparison between raw inter-rater variation and post-standardization agreement. Blinding of bedside raters, EEG readers, adjudicators, and the statistical team should limit expectation effects and incorporation bias. The adjudicated reference will integrate structured behavioral observations, available video, nursing observations, medication exposure, airway status, body position, and other confounders, reflecting the clinical reality that a single bedside score may not capture the highest reproducible behavior. This design is aligned with SPIRIT-AI principles, which emphasize transparent reporting of intervention components, human-AI interaction, handling of errors, and procedures for monitoring algorithm performance (33).

The study has limitations. It is single-center, and its findings may be influenced by local patient mix, EEG equipment, assessment culture, rehabilitation workflow, and adjudication practice. The reference standard is expert-adjudicated but still behaviorally anchored, and it cannot fully resolve covert consciousness detected only by specialized task-based neuroimaging or electrophysiology (2, 4, 6). Video availability may vary according to consent and local policy. EEG artifacts and clinical instability are expected in this population, and fallback to report-level EEG variables may reduce model precision. Finally, because the system will operate in read-only mode, this validation study will assess standardization accuracy, feasibility, and safety signals, not whether AI-assisted scoring improves downstream treatment decisions or patient outcomes.

If successful, the study may provide a reproducible framework for human-supervised AI-assisted CRS-R score standardization. Its most plausible near-term role would be to flag cases requiring repeat assessment, expert review, or closer scrutiny of confounding conditions, particularly when model uncertainty is high or when standardized scores differ substantially from raw bedside scores. Such a use case would be consistent with the current maturity of EEG-based and AI-based approaches in DoC, where decision support and standardization are more defensible than autonomous diagnosis (1, 5, 30).

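### The eligibility criteria and primary analysis population do not keep model-development patients out of the prospective validation cohort

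*Protocol article*

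**What the plan says.** The Discussion describes the study in these terms: "It is single-center, and its findings may be influenced by local patient mix". Section 2.1 names one hospital for the whole two-stage study and gives no separate source for the development records.

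Section 2.2 states, with the qualifier that this holds whenever applicable, that "the retrospective model-development and prospective-validation cohorts will follow the same prespecified inclusion and exclusion criteria". The list in 2.2.2 opens with "Participants will be excluded if any of the following applies" and gives eight items. They concern sedation, paralysis, other disease, EEG quality, skull defects, acute reversible illness and consent. None concerns earlier use of the patient's data in development.

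Three safeguards bear on the separation of training and test data:
- Section 2.3: "The model will be fully trained and locked before the first prospective participant is included".
- Section 2.3.5, for nested cross-validation during retrospective development: "If a patient contributes more than one assessment episode, all episodes from that patient will remain in the same fold".
- Section 2.3.5, for the prospective stage: "No parameter updating, threshold tuning, or online learning will be allowed during prospective validation".

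Section 2.10 defines who counts in the primary test: "The primary analysis population will include participants with two blinded bedside CRS-R assessments, usable EEG according to protocol, and an adjudicated reference score". Its sensitivity analyses drop participants for clinical change between ratings, missed timing targets, and sedation or airway changes, but not for overlap with the development data.

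**The concern.** The prospective stage is meant to show how a locked model performs outside the conditions under which it was developed. That needs test patients who are independent of the training patients. The protocol accepts this principle within development, where all episodes of one patient stay in one fold, but does not carry it across the boundary between development and validation.

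Under the criteria as written, a development patient who is still an inpatient or is readmitted, still has a qualifying diagnosis and is consented could be enrolled and counted in the primary analysis. The model inputs include fairly stable patient characteristics (age, sex, etiology, airway status, motor and language impairment, in 2.3.1) as well as EEG features. Flexible learners such as gradient boosting and random forests are candidates (2.3.4). Such a model may do better on a patient it was trained on than on a new one. The same concern reaches category agreement, subscale agreement and the uncertainty-flag results.

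**Working it through.** **1. Does any stated rule close the gap?**

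| Rule | What it prevents | Bars a development patient from the primary analysis? |
|---|---|---|
| Lock before first inclusion (2.3) | Prospective data shaping the model | No; it separates the stages in time, not by patient |
| Patient-level folds (2.3.5) | One patient in both training and held-out folds | No; retrospective cross-validation only |
| No updating or tuning (2.3.5) | The model changing during validation | No |
| Inclusion and exclusion lists (2.2.1, 2.2.2) | Clinically unsuitable cases | No |
| Primary population and sensitivity analyses (2.10) | Incomplete or unstable cases | No |

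**2. Where would overlap act on the endpoint?** Equations 1 to 3 give D_i as the mean over two raters of raw error minus AI error. Prior training on the patient can change only the AI term. If the reference score is close to what it was at training, a pull toward the old score lowers AI error and raises D_i. If the patient has clearly improved or worsened, the same pull can raise AI error and lower D_i.

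**3. How large could it be?** Let f be the share of analyzed participants who were development patients and b the average extra D_i in them. The shift in the mean of D_i is f × b. The article gives neither value, so the figures below only illustrate a range. The rejection rate is for a true mean of zero, using 98 evaluable participants and an SD of 2.5 (section 2.9), so the standard error is 2.5/√98 = 0.253, with a normal approximation.

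| f | b (points) | Shift f × b | Two-sided 5% test rejects |
|---|---|---|---|
| 5% | 1 | 0.05 | 5.5% |
| 10% | 1 | 0.10 | 6.8% |
| 20% | 1 | 0.20 | 12.4% |
| 10% | 2 | 0.20 | 12.4% |
| 20% | 2 | 0.40 | 35% |

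The planned effect is 1.0 point. For given f and b the shift does not shrink as more participants are recruited. There is also a ceiling: AI error cannot fall below zero, so D_i cannot exceed the participant's mean raw error. The document does not show whether that leaves room for b = 1 or 2.

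**4. Can the study afford to leave such patients out?** Section 2.9 states 98 evaluable participants for a mean difference of 1.0, SD 2.5, two-sided alpha 0.05 and 80% power. The paired formula gives (2.5 × (1.960 + 0.842)/1.0)² = 49.1, so 50, or 52 with the exact t distribution. The stated 98 is not reproduced that way; that is a separate matter, used here only to judge the spare power. With 120 recruited and 15% attrition, 120 × 0.85 = 102 are evaluable. On the article's own effect and SD:

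| Overlap removed | Evaluable left | Power (paired t) |
|---|---|---|
| 5% | 96 | 97% |
| 10% | 91 | 97% |
| 20% | 81 | 94% |
| 30% | 71 | 91% |

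To hold 98 evaluable participants who are all new to the model would take 98/0.85/(1 − f): 122, 129, 145 or 165 recruited.

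**The case against.** The case against has real force. This is an argument from silence in a condensed article. Sharing clinical criteria between cohorts is sound practice, and the whenever-applicable qualifier leaves room for differences. A full protocol may hold the rule. Figure 1, whose caption speaks of a route-separated framework, is not shown. That the development records come from this hospital is inferred from the setting and the single-center statement. A prospective case also brings a new EEG, new ratings and a newly adjudicated reference, so no training record is reused as such.

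A reader might infer that overlap is expected, because chronicity is a planned subgroup. That does not follow: the recorded variable is time since injury, not length of stay, and a chronic patient may be newly admitted. Nor do several episodes per patient in development show it, since that provision is conditional and concerns development only. A reader might also take the protocol to promise testing only on unseen patients; it does not say so in those terms.

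What remains is that eligibility and the primary population are matters this article does set out, and as set out they admit a training patient to the primary test. None of the stated safeguards addresses that.

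**Conclusion.** The gap is real: as written, a patient used in development can enter the prospective cohort and count in the primary analysis. It would be too strong to say that the validation is contaminated, or that the result is bound to favour the AI. Overlap is possible but not shown, and bias toward the AI requires that the patient's state be largely unchanged since training. The shifts of 0.05 to 0.40 points shown above rest on assumed values of f and b, and the upper end needs both to be high. The document supports no estimate of its own. This should be fixed because the remedy is cheap and protects the independence on which a locked-model test depends; it does not by itself invalidate the design.

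**What to change.** Add to 2.2.2, for the prospective cohort only, an exclusion for any patient with an EEG or CRS-R episode used in model development, tuning or threshold setting. Check it at screening against the archived list of development patient identifiers.

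Alternatively, keep such patients in the feasibility population, report how many there are, and restrict the primary analysis in 2.10 to patients new to the model.

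The cost is one criterion and one identifier check. A few patients become ineligible and recruitment may be slightly slower. If a rule of this kind already stands in a fuller protocol, stating it in 2.2 is enough.

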#### EEG acquisition and preprocessing

2.3.3

Routine scalp EEG will be recorded using the international 10–20 system with at least 19 channels. The minimum sampling rate will be 256 Hz, with higher sampling rates preserved when available. The target recording duration will be at least 20 min. The target analysis segment will be an eyes-open or resting unstructured bedside recording obtained without active command-following tasks. If eyes-open recording is not feasible, the observed eye state, arousal condition, recent stimulation, and nursing or respiratory events will be documented.

EEG preprocessing will use a prespecified locked pipeline: channel inspection, removal of non-physiological or disconnected channels, bad-channel interpolation when appropriate, band-pass filtering from 0.5 to 45 Hz, 50-Hz notch filtering when line noise is present, common average or linked-mastoid re-referencing according to the locked acquisition montage, artifact detection and rejection, and extraction of artifact-reduced analysis epochs. Quantitative analysis will use 4-s epochs with 50% overlap. The minimum analyzable duration will be 5 min of artifact-reduced EEG. Epochs will be rejected when any channel shows absolute amplitude greater than 500 μV, flat signal below 1 μV for at least 5 s, abrupt step change greater than 200 μV, visually confirmed electrode-pop or movement artifact, or high-frequency muscle contamination defined as 20–45 Hz power more than three standard deviations above the recording median. Recordings with more than 30% bad channels or less than 5 min of acceptable EEG after artifact rejection will be classified as quantitative-EEG failures. The final software implementation, reference montage, and quality-control log format will be archived with the locked preprocessing package before prospective enrollment.

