### Missing data

2.11

The adjudicated reference score will not be imputed. Missing clinical contextual covariates required for inference will be handled by the locked preprocessing pipeline, including explicit missingness indicators where applicable. Missing-data handling rules will be estimated or fixed within training folds during retrospective development and locked before prospective validation. If quantitative EEG features cannot be extracted but report-level EEG variables are available and the locked fallback pathway is triggered, the case will remain analyzable. Cases lacking both usable quantitative EEG and report-level EEG information will be counted as technical failures for the primary analysis and retained in feasibility summaries.

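### As written, nothing brings failed-EEG cases into the data on which the report-level fallback is fixed, and the planned reduced-feature test is not tied to cases that trigger it

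*Protocol article*

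**What the plan says.** Section 2.2 (Study population) states, with the qualifier that this holds whenever applicable: "the retrospective model-development and prospective-validation cohorts will follow the same prespecified inclusion and exclusion criteria".

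Section 2.2.2 (Exclusion criteria) excludes "EEG recordings of insufficient quality despite repeat acquisition when repeat acquisition is clinically feasible". A separate criterion excludes "EEG dominated by uncontrolled epileptiform activity or status epilepticus, preventing valid resting-state background or connectivity feature extraction".

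Section 2.3.3 (EEG acquisition and preprocessing) gives a numerical rule: "Recordings with more than 30% bad channels or less than 5 min of acceptable EEG after artifact rejection will be classified as quantitative-EEG failures". It calls these failures and does not say that they are excluded.

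Section 2.11 (Missing data): "If quantitative EEG features cannot be extracted but report-level EEG variables are available and the locked fallback pathway is triggered, the case will remain analyzable". Only cases lacking both EEG sources are technical failures for the primary analysis. The same section fixes the missing-data rules in the retrospective training folds and locks them. Section 2.3.5 allows no tuning afterwards.

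Section 2.10 (Statistical analysis) limits the primary population to participants whose EEG is usable under the protocol. It adds: "A reduced-feature inference mode using report-level EEG variables only will also be tested". No population is named for that test, and none of the listed subgroup or sensitivity analyses splits results by inference mode.

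**The concern.** A fallback should be built and checked on the kind of case that triggers it. Here the default eligibility rule points the other way. If the insufficient-quality criterion is applied to the retrospective cohort, the episodes that resemble future fallback cases leave it. What remains for setting the fallback rules is patients whose quantitative features exist and are ignored.

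Those are not necessarily the same kind of patient. Section 2.3.3 rejects EEG for movement, muscle contamination, flat signal and electrode faults. Some of these causes are technical, but movement and muscle artifact may plausibly go with motor and arousal state, which the protocol itself treats as sources of score variability. Accuracy with features withheld in good-EEG patients need not carry over to true failures.

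At stake is mainly what can be concluded about the fallback. The Discussion accepts that falling back may cost precision, but the text describes no check in the patients affected. Once the model is locked, section 2.3.5 rules out a correction.

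**Working it through.** **Setting the sections side by side**

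| Question | Development cohort | Prospective cohort |
|---|---|---|
| Insufficient-quality EEG excluded? | Yes by default (2.2 with 2.2.2), subject to the qualifier in 2.2 | Yes (2.2.2) |
| Failed quantitative EEG with a report kept? | Not stated | Yes, analyzable through the fallback (2.11) |
| Counts as usable EEG for the primary population? | Not applicable | Not stated (2.10) |
| Role in the fallback | Rules fixed here, then locked (2.11, 2.3.5) | Rules applied here |

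The provision that retains failed-EEG cases in 2.11 is framed around the primary analysis and the feasibility summaries, which belong to the validation stage. No matching sentence covers development.

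**The reduced-feature test.** Let f be the share of participants who trigger the fallback. If the test is run on everyone, a share 1 - f have usable quantitative EEG. At an assumed f of 5-10%, 90-95% of the result comes from participants who do not need the fallback.

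**Plan figures used.** The plan gives no EEG-failure rate. The nearest figure is the allowance of about 15% attrition from all causes in section 2.9: 98 / 0.85 = 115.3, so 116, and the target of 120 leaves 120 x 0.85 = 102. That allowance also covers incomplete assessments, missing videos and withdrawal, and it counts participants lost to analysis. It is not a rate of fallback use. (The 98 is taken as stated. The paired formula with the plan's inputs gives (2.5 x (1.960 + 0.842) / 1.0)^2 = 49.1, so 50. That is a separate matter and does not bear on this point.)

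**Size of the effect on the primary mean (assumed f; assumed 1-point worse error reduction in fallback cases).** Shift in mean D = f x 1 point.
- f = 5%: 0.05 x 120 = 6 participants; shift 0.05.
- f = 10%: 0.10 x 120 = 12 participants; shift 0.10.

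For comparison, the plan assumes a mean reduction of 1.0, and the standard error of the mean at the planned size is 2.5 / sqrt(98) = 0.25.

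**What the prospective data alone could show about the fallback.** Taking the plan's SD of 2.5 to hold in this group, the 95% half-width is 1.96 x 2.5 / sqrt(k).
- k = 6: 2.0 points.
- k = 12: 1.4 points.

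Both exceed the 1.0-point effect that the trial is designed to detect. Retrospective failure episodes are therefore the main other source of evidence.

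**The case against.** The strongest reply has four parts.

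**The qualifier.** Section 2.2 says the criteria are shared only where applicable, and a criterion that depends on repeating a recording may not suit archived data. This stands as a caution: the exclusion is a default for development, not a certainty. It does not settle the matter, because EEG quality can be judged from archived recordings and no exemption is named.

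**Symmetry.** The same criterion governs both cohorts. If it removes all failures, no prospective fallback cases remain; if it leaves some, it leaves some in development too. This has force, especially as 2.2.2 does not equate insufficient quality with the failure rule in 2.3.3. But 2.11 expressly keeps such cases at the validation stage and says nothing comparable for development.

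**Silence is not a flaw.** The article is condensed, Figure 1 (captioned as route-separated) and Algorithm 1 are not reproduced, and development details are deferred to a later report. This stands against one tempting inference: a reader might conclude that the fallback is built only on patients who never need it. The documents do not say on whom it is trained. They support only the statement that, as written, nothing brings failure cases in.

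**The reduced-feature test.** A reader might infer that this test repeats the problem. Its population is not given, and the plan does not call its result fallback performance, so that too is conditional. What stands is that the test is not restricted to triggered cases.

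**Conclusion.** The point holds in a limited form. The shared criteria, by default, carry the EEG-quality exclusion into development, while the validation stage relies on a locked fallback for cases of that kind. The one planned test of report-level inference is not tied to them.

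The effect on the primary result is unknown and probably small: 0.05-0.10 points if 5-10% of participants use the fallback and do 1 point worse, both figures being assumptions. A reader might infer that fallback scores certainly enter the primary endpoint, or that up to 15% of participants are affected. Neither is supported. Section 2.10's requirement of usable EEG leaves the first open, and the 15% is all-cause loss to analysis. The practical consequence is that any accuracy figure for the fallback might not describe the patients who need it. The change should be made before lock.

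**What to change.** 1. **Section 2.2:** state that the insufficient-quality EEG exclusion does not remove development episodes that have report-level EEG variables and a reference score. Use these episodes inside the training folds for the fallback. Report their number and their outer-fold error before lock.
2. **Section 2.10:** report the participant-level error reduction and the absolute error by inference mode actually used. Label the report-level-only run in participants with usable quantitative EEG as an ablation, not as fallback performance.
3. **Sections 2.2.2, 2.10 and 2.11:** reconcile them on whether fallback cases belong to the primary population.

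The cost is modest: existing retrospective records, some extra analysis and a few sentences of text. The downside is that failure episodes with both a report and a reference score may be few, so the estimates will be imprecise. In that case the number itself is worth reporting, because it shows how little supports the fallback.
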